## Methods: data collection, management, and analysis

### Data collection and statistical methods

The primary efficacy analysis will assess average treatment group differences for the primary outcome measure BACS, over the entire study period (baseline, post-intervention, follow-up), and will use a likelihood based mixed-effects model, repeated measures (MMRM) approach. The MMRM model includes the fixed, categorical effects of treatment (CCT or CIRCuiTS), visit (baseline, 12 and 24 weeks), and treatment-by-visit interaction, as well as the continuous, fixed covariates of baseline score and baseline score-by-visit interaction. The MMRM includes all available data at each time point and is the preferred method of analysing clinical trial data in psychiatry as compared to more traditional repeated measures analysis of variance (ANOVA) and analysis of covariance (ANCOVA) models. Planned comparisons will be done with the MMRM models to determine between-group differences in change of symptoms measures from baseline to weeks 12 and 24. Results from the analysis of dichotomous data will be presented as proportions, with 95% confidence interval, and Fisher’s exact *p* value where appropriate. Non-parametric statistics will be used when assumptions for parametric methods are violated. Effect sizes will be calculated using Cohen’s guidelines. All tests of treatment effects will be conducted using a two-sided alpha level of 0.05 and 95% confidence intervals.

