### Trial design

The design is a single-blind, randomised controlled trial to examine the equivalence of CCT and CIRCuiTS. The trial also aims to examine if MMN at baseline can predict response to the compensation and adaptation therapies and if MMN improves from baseline to post-treatment.

The study will include 100 clinically stable patients with a schizophrenia spectrum disorder. Participants will be randomised in a 1:1 ratio to join either the CCT group or the CIRCuiTS group. Participants will all be active cases in Metro South Addiction and Mental Health Services (community based). Participants in the study will continue to receive standard clinical care (i.e. there are no restrictions on medication or psychosocial interventions, apart from participants receiving therapies addressing neurocognition). These two interventions will be delivered by trained mental health staff once (CCT 2-h session) or twice (CIRCuiTS 1-h sessions) per week for 12 weeks. Groups will be based on a maximum of 6 participants per facilitator. Individual clinical assessments will be at baseline, at post-treatment, and at 3-month follow-up. Randomisation will be carried out using a computer-generated randomisation table.

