## Methods: assignment of interventions

### Allocation and blinding

A minimum of twelve participants will be recruited for each round of the study. Participants will be recruited and randomly allocated in block sizes of four using randomisation procedure Statistical Analysis System (SAS) 9.4 by a member of the research team not involved in the delivery of the intervention or outcome assessment. As participants may drop out of therapy, the group numbers may fall to no lower than two participants. The therapeutic group size is two to six participants. Information about the treatment allocation will be emailed to the therapists who will contact participants about their therapy.

A battery of validated clinical measures will be conducted by trained research assistants, who are blind to group membership, at baseline, post-intervention, and 3-month follow-up. The research staff who undertake the outcome assessments will be blind to group allocation and will advise participants not to reveal their treatment. If a patient reveals this information, this will be noted for post hoc analyses of the data.

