## Discussion

Compensation and adaptation therapies have been demonstrated to improve neurocognitive functioning in people with schizophrenia spectrum disorders. The current study aims to evaluate the equivalence of two different compensation and adaptation therapies (CIRCuiTS and CCT) within a community mental health service. This study also aims to identify if mismatch negativity can predict an individual’s response to compensation and adaptation therapies. This knowledge will allow clinicians to identify individuals who are more likely to receive benefit from a compensation and adaptation therapy programme.

This RCT has several strengths. To date, no other study has incorporated neurophysiological measures of mismatch negativity to identify participants that may be more likely to benefit from compensation and adaptation therapies. This is a novel approach and may assist with identifying future participants of compensation and adaptation therapy programmes. Participants will be randomly assigned to each group, and the raters remain blind to condition to avoid bias. A variety of outcome measures will be used to assess functioning across neurocognitive, social, and neurophysiological domains.

No formal assessment of inter-rater reliability will be conducted. Groups will be matched for total exposure to therapy (2 h per week over 12 weeks). Participants in the CIRCuiTS group may not have completed all 40 phases prior to the post-intervention assessments. Clinician effects may influence the results as one therapist will deliver CCT and one will deliver CIRCuiTS.

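### Both therapies are delivered in small groups, but the primary model names no term for therapy group, so any within-group correlation would make the interval for the treatment difference too narrow

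*Protocol article*

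**What the plan says.** Group delivery applies to both arms. Protocol article, Trial design: "Groups will be based on a maximum of 6 participants per facilitator". Allocation and blinding: "The therapeutic group size is two to six participants"; the Participant timeline section gives the same range. Groups form in successive rounds: "A minimum of twelve participants will be recruited for each round of the study".

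The unit of randomisation is the individual. "Participants will be recruited and randomly allocated in block sizes of four" (Allocation and blinding), and "Participants will be randomised in a 1:1 ratio to join either the CCT group or the CIRCuiTS group" (Trial design). The clustering therefore arises after randomisation.

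The primary model is set out under Data collection and statistical methods: "The MMRM model includes the fixed, categorical effects of treatment (CCT or CIRCuiTS), visit (baseline, 12 and 24 weeks), and treatment-by-visit interaction". The only other terms named there are the BACS value at baseline and its interaction with visit. It is called a likelihood-based mixed-effects model. Neither this section nor Sample size mentions correlation between members of a therapy group; Sample size uses group size only as a practical limit on the total of 100.

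The Discussion makes one related concession: "Clinician effects may influence the results as one therapist will deliver CCT and one will deliver CIRCuiTS".

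**The concern.** An MMRM handles correlation between repeated measurements on the same participant. It does not handle correlation between different participants who sit in the same therapy group for 12 weeks. If that correlation is positive and no term captures it, the model counts more independent information than the trial holds, and the interval for CCT versus CIRCuiTS comes out too short.

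Interval width matters here because the primary objective is equivalence. Under the usual rule, where the whole interval must lie inside a margin, an interval that is too short makes a false claim of equivalence more likely. The abstract says the result bears on services where cost and lack of computers limit such programmes, so a false claim could influence which programme they adopt.

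**Working it through.** **Inputs from the Protocol article.** Total 100; dropout 15–20%; about 80 completers (Sample size). Rounds of at least twelve, 1:1 allocation, groups of two to six (Trial design; Allocation and blinding). Two-sided alpha 0.05 and 95% confidence intervals (Data collection and statistical methods).

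**The plan's own figure.** 100 × (1 − 0.20) = 80 and 100 × (1 − 0.15) = 85. The stated figure of about 80 is reproduced at the 20% end.

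**Group size at analysis.** 100 / 12 ≈ 8 rounds; 8 × 2 arms = 16 groups if each round has one group per arm; 80 / 16 = 5 completers per group.

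**Assumption.** No ICC is documented. I use 0.01 to 0.10, the same in both arms, with equal group sizes. The calculation is for one post-baseline time point, without baseline adjustment.

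**Formulas**, with m = 5 and n = 80:
- design effect DE = 1 + (m − 1) × ICC
- ratio of correct to reported interval width = √DE
- effective n = 80 / DE
- true coverage = 2Φ(1.96/√DE) − 1
- true error per side = 1 − Φ(1.96/√DE)

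| ICC | DE | Width ratio | Effective n | Coverage | Error per side (nominal 2.5%) |
|---|---|---|---|---|---|
| 0 | 1.00 | 1.000 | 80.0 | 95.0% | 2.5% |
| 0.01 | 1.04 | 1.020 | 76.9 | 94.5% | 2.7% |
| 0.02 | 1.08 | 1.039 | 74.1 | 94.1% | 3.0% |
| 0.05 | 1.20 | 1.095 | 66.7 | 92.6% | 3.7% |
| 0.10 | 1.40 | 1.183 | 57.1 | 90.2% | 4.9% |

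In SD units the 95% half-width under independence is 1.96 × √(2/40) = 0.438. Multiplied by the width ratio, it becomes 0.447, 0.480 and 0.519 at ICC 0.01, 0.05 and 0.10.

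**Simulation check.** Eight groups of five per arm, analysed as independent, 40,000 runs: coverage was 95.0%, 94.5%, 92.6% and 90.3% at ICC 0, 0.01, 0.05 and 0.10, in line with the formula.

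**Sensitivity to group size.** With m = 4, DE runs from 1.03 to 1.30 and coverage from 94.7% to 91.4% over ICC 0.01 to 0.10. With m = 2, DE does not exceed 1.10.

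**Correlation in CCT only.** The variance of the difference uses the average of the two arms' design effects: (1.20 + 1.00)/2 = 1.10 at ICC 0.05 and (1.40 + 1.00)/2 = 1.20 at ICC 0.10. Coverage is then 93.8% and 92.6%.

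**The case against.** **Only the fixed part of the model is published.** The section names fixed effects and fixed covariates of a mixed-effects model and gives no random effect or covariance structure at all. A reader might infer that the plan has positively assumed independence. It has not said so, and an analysis plan not shown could add a group term. What stands is narrower: the published specification names nothing for therapy group, although the same article describes group delivery in both arms, and an analyst following it as written would leave the group out.

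**The size is unknown.** This stands. A reader might infer that the interval is too narrow as a matter of fact. That needs a positive ICC, which the documents do not supply. At 0.01 to 0.02 the effect is slight. CIRCuiTS is computer-delivered with flexibly chosen tasks, so its within-group correlation may be weaker than that of CCT.

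**Some shared influences do not shorten the interval.** This also stands. The lead therapist is the same for every group in an arm, so a therapist effect shifts the arm mean and adds no within-group correlation beyond it. Calendar time is shared by both arms of a round and largely cancels in the difference. Whether the two arms of a round share a site is not stated. Peers, group dynamics and co-facilitators remain.

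**The direction of harm depends on the decision rule.** The protocol states no equivalence margin. If equivalence were read from a non-significant difference, a standard error that is too small would make that claim less likely, not more. The false-equivalence argument holds only for an interval-within-margin rule. A reader might also apply a 5% one-sided error, which would give larger figures, but the protocol specifies 95% intervals, for which the nominal rate is 2.5% per side.

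**Therapist and arm are confounded.** The Discussion discloses this, and no model term can separate the two. It is not part of this point.

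**Conclusion.** The concern holds in conditional form and is worth correcting. Both arms are group-delivered, and the primary model as published names no term for the group. If outcomes correlate positively within groups, the standard error and 95% interval for the between-arm difference will be too small.

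Under the stated assumptions the correct interval is about 2% to 18% wider than the one reported. The upper end needs an ICC of 0.10 in both arms, and the range shrinks if groups are smaller or only CCT induces correlation. The per-side error figures of 3.7% and 4.9% apply only if equivalence is judged by the 95% interval against a margin. They describe the inflation of the nominal rate; an error rate or power against an actual margin cannot be computed, because none is given.

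**What to change.** Record the actual therapy group to which each participant is assigned. Round by arm is not a safe substitute: twelve is a minimum round size, so a round may contain more than one group per arm.

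Add a random effect for that group to the primary model, acting on the post-baseline visits only. The model lists baseline as a visit, and a constant group intercept would impose clustering at a time when the groups did not yet exist. Use Kenward-Roger or similar small-sample degrees of freedom, and analyse by assigned group regardless of attendance.

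The cost is one data field, already known to the therapists, and one variance component estimated from about 16 groups. Recruitment and treatment do not change. The interval will be wider, and not necessarily by a little: the treatment contrast may rest on about 16 − 2 = 14 degrees of freedom. If the estimated group variance is close to zero, the results should change little.

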### Objectives

This study will use a randomised controlled trial to test the equivalence of CCT compared with CIRCuiTs to address the cognitive deficits of schizophrenia spectrum disorders. The primary objective is to examine the equivalence of CCT in improving neurocognitive deficits in people with schizophrenia spectrum disorders compared with CIRCuiTS. The secondary objective examines if CCT and/or CIRCuiTS are associated with objective and subjective improvement in community and cognitive functioning. In addition, we aim to determine whether MMN at baseline can be used to predict on an individual level, who might benefit from either treatment.

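### The primary mixed model uses baseline BACS as both response and covariate and averages the group difference over the baseline visit, shrinking estimate and interval by a third, which favours a finding of equivalence

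*Protocol article*

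**What the plan says.** All the model statements are in the protocol article, Data collection and statistical methods.

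- **Primary effect:** "average treatment group differences for the primary outcome measure BACS, over the entire study period (baseline, post-intervention, follow-up".
- **Model terms:** treatment, "visit (baseline, 12 and 24 weeks), and treatment-by-visit interaction, as well as the continuous, fixed covariates of baseline score". The covariates in full are the "fixed covariates of baseline score and baseline score-by-visit interaction".
- **Rows used:** "The MMRM includes all available data at each time point". With baseline a level of visit, the baseline scores enter as responses.
- **Planned comparisons within the model:** "between-group differences in change of symptoms measures from baseline to weeks 12 and 24".
- **Inference:** "All tests of treatment effects will be conducted using a two-sided alpha level of 0.05 and 95% confidence intervals".

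Under Objectives: "The primary objective is to examine the equivalence of CCT in improving neurocognitive deficits". The article states neither an equivalence margin nor a covariance structure.

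**The concern.** A baseline measurement can be one of the repeated responses or an adjustment covariate. Here it is both. At the baseline visit the model then regresses a variable on itself, so there is nothing left to estimate and no residual variation.

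The primary effect also averages over a visit at which no treatment has been given. In this model the difference at that visit is zero by construction, and it pulls the average towards no difference. In a superiority trial this would mostly be a matter of scaling. In an equivalence trial the interval is compared with a fixed margin, so the scaling acts in favour of the claim the trial sets out to make.

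**Working it through.** **Inputs from the article.** 100 randomised 1:1 (Trial design, Sample size); dropout 15–20% and about 80 completers (Sample size); three visits; 95% intervals. The completer figure reproduces at the upper dropout rate: 100 × (1 − 0.20) = 80, and 100 × (1 − 0.15) = 85 at the lower. I use 40 per arm with complete data.

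**Assumptions, not in the article.** SD 1 at every visit; a common correlation ρ of 0.5 to 0.8 between visits; a true difference of 0.30 SD at both weeks 12 and 24; equal visit weights in the average; where a margin is needed, 0.30 SD.

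**1. Baseline rows.** At visit v the model is Y_v = α_v + τ_v·T + β_v·B + e_v, where T is treatment and B is baseline BACS. At baseline Y_0 = B, so α_0 = 0, τ_0 = 0, β_0 = 1 fits every row with e_0 = 0. Simulation (4,000 trials per scenario) agrees: baseline treatment coefficient below 2e-16, baseline residual variance about 1e-33. An unstructured covariance matrix then has a zero variance and is singular.

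**2. The averaged effect.** (0 + d12 + d24)/3 = (2/3) × (d12 + d24)/2. With 0.30 at both visits, 0.60/3 = 0.20 SD instead of 0.30 SD. The factor 2/3 does not depend on SD, correlation or margin.

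**3. Its standard error.** The baseline-adjusted variance of the week 12 and 24 average is [(1 + ρ)/2 − ρ²] × 2/40. The three-visit average is 2/3 of that quantity, so its SE is 2/3 as large.

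| ρ | SE, weeks 12 and 24 | SE, three visits |
|---|---|---|
| 0.5 | √(0.50 × 0.05) = 0.158 | 0.105 |
| 0.7 | √(0.36 × 0.05) = 0.134 | 0.089 |
| 0.8 | √(0.26 × 0.05) = 0.114 | 0.076 |

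**4. Test of zero difference.** Both parts of the ratio shrink alike: at ρ = 0.7, 0.20/0.0894 = 0.30/0.1342 = 2.24. The t-statistic is unchanged.

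**5. Coverage of the post-baseline difference.** The interval is centred 0.10 too low. With k = 0.10/SE, coverage is Φ(1.99 − k) − Φ(−1.99 − k).

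- ρ = 0.5: k = 0.95, coverage 85%
- ρ = 0.7: k = 1.12, coverage 81% (simulation 81%)
- ρ = 0.8: k = 1.32, coverage 75%

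**6. Effect on an equivalence decision.** Put the true difference on an assumed margin of 0.30 SD with ρ = 0.7. The diluted interval lies inside the margin when Z < (0.10 − 1.99 × 0.0894)/0.0894 = −0.87, a probability of 19%. The simulation gave 19%, against 2% for the week 12 and 24 average.

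**7. Other contrasts.** The change contrast at week 12 is d12 − 0 = d12, so it is not diluted. At ρ = 0.8 under compound symmetry its model SE was 0.137 against a sampling SD of 0.135, with coverage about 95%. Over the scenarios run, this SE ranged from 7% too small to 6% too large under compound symmetry. A raw week-12 least-squares mean difference behaves differently: one visit in three has zero residuals, so the pooled variance falls to about 2/3 and the SE to √(2/3) = 0.816 of its proper size. At ρ = 0.8 that gave 0.110 against 0.135, with coverage about 90%.

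**The case against.** **The test is unaffected and no margin is stated.** The article specifies two-sided tests at 0.05, and their p-value does not change. That stands. The stated objective is nevertheless equivalence, and any margin would be set on the scale of a real post-treatment difference. The false-equivalence rate depends on assumed values; the factor 2/3 does not.

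**The standard error is not wrong for its own target.** A reader might infer that the reported intervals are invalid. The documents do not support that for either contrast they name. The period average covers its own diluted target at about 95%, and the week-12 change contrast also covers at about 95% in the setting shown. Only a raw visit-specific mean difference has an SE 18–20% too small. The article does not name that contrast, and the error arises under compound symmetry, which the article does not state. Under an unstructured covariance the symptom would be a singular fit, which is a visible failure.

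**The undiluted change contrasts limit the harm.** They do, if the phrase about symptom measures is read to include BACS. But they are planned comparisons alongside the primary analysis and do not replace it.

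**The full analysis plan may settle it.** Covariance structure and software detail can be left there. The visit levels, covariates and averaging window, however, are stated outright, and a later plan could correct them only by departing from this text.

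**Conclusion.** Wrong as written. Baseline BACS cannot be both response and covariate with a visit interaction, and a primary treatment effect should not average in a pre-treatment visit. With equal weights and complete data, the estimate and its interval are exactly 2/3 of the post-baseline ones. Against any fixed margin this favours declaring equivalence. With an assumed true difference of 0.30 SD, 40 per arm and correlations of 0.5 to 0.8, the interval covers the post-baseline difference about 75–85% of the time. With that difference on an assumed 0.30 SD margin and correlation 0.7, false equivalence is about 19% instead of 2%.

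Two stronger readings do not hold. The narrow interval is not a second, independent error: for the primary average, estimate and SE are rescaled together. Nor does the article leave three rival primary contrasts, since it calls the period average primary and the week 12 and 24 contrasts planned comparisons.

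**What to change.** Choose one of two standard forms:

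- use weeks 12 and 24 as the only responses, keeping baseline BACS and baseline-by-visit as covariates; or
- keep baseline as a response with a mean common to both arms, and drop the baseline covariates.

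In either case, remove baseline from the averaging window and define the primary contrast on post-baseline visits only. The average of weeks 12 and 24 is legitimate, and so is one named visit; which of these to use is the investigators' choice. State the covariance structure at the same time.

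The cost is one paragraph in the protocol or analysis plan, made before the data are analysed. No new data are needed.

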### CIRCuiTs

CIRCuiTS (Computerised Interactive Remediation of Cognition–Training for Schizophrenia) is a modular package including tasks of a wide range of cognitive functions (particularly executive function and memory), intended to allow therapy programmes to be flexibly designed to incorporate only relevant tasks. Prior to attempting a task, the participant needs to register how long they believe the task will take, how difficult the task is expected to be, and the strategy they intend to use. They receive computer feedback on these dimensions and re-rate how useful the strategies were with the goal of developing metacognitive knowledge and awareness. CIRCuiTS is run for 1 h twice a week and is delivered through a computer. The CIRCuiTS programme used consists of 40 stages. The tasks are progressively more difficult as the participant works through the programme. Twenty sessions are considered an adequate treatment exposure.

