### Sample size

In this equivalence study, we will focus on the primary outcome of cognition. We based our power analysis specifically on the BACS. We estimate a dropout rate of 15–20% (from treatment to 3-month follow-up) resulting in a final sample size of approximately 80 participants who will complete the study. This estimate is based on the dropout rates for studies with participants with serious mental illness as well as our experience with group randomised controlled trial research. Due to practicalities of group size and opportunities for running groups over the study timeframe, the maximum number of participants was set at one hundred.

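### The primary aim is equivalence, but the stated primary analysis is a two-sided test of difference with no margin and no rule for concluding equivalence

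*Protocol article*

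**What the plan says.** Under Objectives, the protocol article states: "The primary objective is to examine the equivalence of CCT in improving neurocognitive deficits in people with schizophrenia spectrum disorders compared with CIRCuiTS". Trial design describes a "single-blind, randomised controlled trial to examine the equivalence of CCT and CIRCuiTS". The Sample size section and the Discussion also present the study as one of equivalence, and the Outcomes section names the BACS as the primary measure.

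Data collection and statistical methods gives the only primary analysis. It is a likelihood-based repeated-measures mixed model that assesses the average difference between treatment groups on the BACS over the study period, with planned comparisons of change to weeks 12 and 24. The inferential standard is: "All tests of treatment effects will be conducted using a two-sided alpha level of 0.05 and 95% confidence intervals".

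Sample size says "We based our power analysis specifically on the BACS" but gives no margin, standard deviation, target power or effect size. It expects about 80 completers after 15–20% dropout and reports that, for practical reasons, "the maximum number of participants was set at one hundred".

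**The concern.** A two-sided test of difference takes no difference as its null hypothesis. Rejecting that null shows that the arms differ. Failing to reject it shows only that the data did not separate them, which also happens when a trial is imprecise. Equivalence requires the reverse: the data must exclude differences large enough to matter, so that size has to be fixed in advance. The article fixes an inferential framework, and it is the one for the opposite question.

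The practical stake is in the abstract's discussion. The result is meant to inform services where cost and lack of computers limit what can be offered. If an imprecise null result were taken as comparable benefit, one programme could be substituted for the other despite losing a good part of the expected gain.

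**Working it through.** **The plan's own figure.** 100 enrolled × (1 − 0.20) = 80 completers, and 100 × (1 − 0.15) = 85. The stated figure of about 80 is reproduced at the 20% end. With 1:1 allocation that is 40 per arm. No power calculation can be reproduced, because its inputs are not given.

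**Inputs for the illustration**
- From the article: 40 completers per arm; two-sided 0.05; 95% CI; a cited meta-analytic effect on global cognition of 0.45 (Background and rationale). The 0.45 serves only as a yardstick. The article does not offer it as a margin.
- Assumed, because the article gives no value: baseline-to-follow-up BACS correlation ρ of 0, 0.7 or 0.8; a single follow-up visit adjusted for baseline; no clustering by therapy group. All differences are in SD units.

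**Standard error.** SE = √(2/40) × √(1 − ρ²)
- ρ = 0: 0.224
- ρ = 0.7: 0.224 × 0.714 = 0.160
- ρ = 0.8: 0.224 × 0.600 = 0.134

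**How often the planned test misses a real deficit.** This is the probability of p > 0.05 from a two-sided t test (77 df, non-centrality = true difference/SE).

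| True difference | ρ = 0 | ρ = 0.7 | ρ = 0.8 |
|---|---|---|---|
| 0.225 SD (half of 0.45) | 83% | 72% | 62% |
| 0.30 SD | 74% | 54% | 40% |
| 0.45 SD | 49% | 20% | 9% |

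**Margin that 40 per arm can support.** For 80% power with two one-sided tests at a true difference of 0, margin = (z for the CI + 1.282) × SE. The z value is 1.645 for a 90% CI and 1.960 for a 95% CI.

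| CI used | ρ = 0 | ρ = 0.7 | ρ = 0.8 |
|---|---|---|---|
| 90% | 2.927 × 0.224 = 0.65 | 0.47 | 0.39 |
| 95% | 3.242 × 0.224 = 0.72 | 0.52 | 0.43 |

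Set against 0.45, the 90% CI margins run from 0.39/0.45 = 87% to 0.65/0.45 = 145% (unrounded, 0.654/0.45) of the whole cited effect. At a margin of 0.225 SD, the 90% CI approach has power max(0, 2Φ(0.225/SE − 1.645) − 1), which is 0%, 0% and 3% for the three correlations.

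**Sensitivity to the planned contrast.** The article's primary contrast is a study-period average, not a single visit. If the two post-baseline visits are averaged and every correlation is 0.7, the variance factor is (1 + 0.7)/2 − 0.7² = 0.36, so SE = 0.224 × 0.6 = 0.134. The 90% CI margin becomes 0.39 instead of 0.47, and a true 0.30 SD deficit is missed 40% of the time instead of 54%. Clustering by therapy group would act in the other direction. The article gives no figure from which to size it.

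**The case against.** The strongest reply has four parts.

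- **The article never says that p > 0.05 will be called equivalence.** This is correct. A reader might infer it, because no other route to the stated conclusion is offered, but no sentence commits to it. What the text supports is that the rule for concluding equivalence is absent and the misreading is left open.
- **The planned 95% interval is sound.** This also stands. Compared with a prespecified margin, a 95% CI is a valid equivalence test at one-sided 0.025. The alpha and interval level are not errors. What is lacking is the margin and the inclusion rule.
- **The article condenses a fuller protocol, which may hold the margin and the power inputs.** For that reason the missing number alone would be a weak point, and one cannot conclude that the trial has no margin at all. The article does, however, state an analysis framework, and that framework does not match its own primary objective. That mismatch is in what is written.
- **The figures are for a simplified analysis.** They are single-visit completer values, whereas the planned contrast is a study-period average using all available data. The figures are illustrative, and the sensitivity check shows how far they move.

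Two further readings are tempting but not supported. One is that the sample size section contradicts itself: a power analysis on the BACS and a practical ceiling on recruitment can coexist, and the text does not say that the former was set aside. The other is that defining adequate exposure only for CIRCuiTS prevents a like-for-like adherence analysis. The article matches both arms at two hours a week for 12 weeks, so an equal share of hours can be applied to each.

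**Conclusion.** The point holds as a mismatch between aim and analysis. An equivalence objective is paired with a two-sided test of difference, with no margin and no rule for claiming equivalence, so the stated test cannot answer the primary question. This conclusion needs no numerical assumption.

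The size of the problem does. With 40 completers per arm, one follow-up visit, ρ between 0 and 0.8 and no clustering, a 0.30 SD deficit goes undetected 40–74% of the time. The smallest margin with 80% power is about 0.39–0.65 SD (90% CI) or 0.43–0.72 SD (95% CI). Averaging visits would narrow these somewhat, and clustering would widen them. On any of these values, a non-significant result would be weak evidence that the programmes are equivalent.

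**What to change.** Before outcomes are compared by arm:

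1. State an equivalence margin for the BACS, in score or SD units, and justify it.
2. For the primary outcome, replace the difference test with confidence-interval inclusion. Equivalence is claimed only if the interval for the adjusted primary mixed-model contrast lies wholly inside the margin. The planned 95% CI can be kept, or a 90% CI used if that is stated as the choice.
3. Say explicitly that a non-significant difference will not be interpreted as equivalence.
4. In the Sample size section, report the margin that about 80 completers can support and the assumptions behind it.
5. If that margin cannot be defended, reword the primary objective as estimating the difference between programmes with its confidence interval.

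The cost is protocol and analysis-plan wording. The stated aim becomes less favourable, since the trial may be able to support only a wide margin or an estimate. No extra patients are needed for either route.
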